# A randomized blinded controlled trial of mobile phone reminders on the follow-up medical care of HIV-exposed and HIV-infected children in Cameroon: study protocol (MORE CARE)

**DOI:** 10.1186/1745-6215-14-313

**Published:** 2013-09-25

**Keywords:** MORE CARE, HIV, AIDS, Children, Attendance, Telemedicine, Short message service (SMS), Phone calls, Resource-limited setting

## Abstract

**Background:**

In Cameroon, only two-thirds of children with HIV exposure or infection receive appropriate HIV-directed medical care. Mortality, antiretroviral therapy resistance and suboptimal virological response are strongly related to missed opportunities for treatment, and, more specifically, to skipped scheduled medical appointments. The present trial, MORE CARE (Mobile Reminders for Cameroonian Children Requiring HIV Care) seeks to determine if reminders sent by text message (SMS), phone call, or concomitant SMS and phone calls most increase the presence at medical appointments of HIV-infected or -exposed children (efficacy), and which is the most efficient related to working time and financial cost (efficiency).

**Methods/Design:**

We will carry out a multicenter single-blind, randomized, factorial controlled trial. A randomization list will be electronically generated using random block sizes. Central allocation will be determined by sequentially numbered. A total of 224 subjects will be randomized into four groups (SMS, Call, SMS + Call, and Control) with an allocation ratio of 1:1:1:1. SMS and calls will be sent between 48 and 72 hours before the scheduled appointment. A medical assistant will send out text messages and will call participants. Our primary outcome is appointment measured by efficacy and efficiency of interventions. We hypothesize that two reminders (concomitant use of SMS and phone calls) as an appointment reminder is more effective to improve appointment compared to one reminder (only SMS or only call), and that the most efficient is use of only SMS. The analysis will be intention to treat.

**Discussion:**

This trial investigates the potential of SMS and phone calls as motivational reminders to improve children’s adherence to medical appointments for HIV-related care in Cameroon. The intervention will act to end missed appointment due to forgetfulness.

## Background

In Central Africa, vertical transmission of human immunodeficiency virus (HIV) infection from mother to child approaches 30%, reflecting in part inadequate implementation of postnatal preventive strategies, especially during breastfeeding [1]. In Cameroon, the number of new pediatric HIV infections was increasing and reached 6,800 in 2011 [2]. Recent estimates indicate that only 13% of children requiring antiretroviral HIV therapy (ART) actually receive it [2]. Inadequate attendance at medical follow-up visits in infancy is a potentially reversible factor. Only 65% of infants born to seropositive mothers presented to the recommended six-weeks-of-age medical visit [3]. Many factors underlie nonattendance at scheduled visits for HIV care and loss to medical follow-up. These include intrapersonal factors such as the cost of transportation, food availability, time constraints due to concomitant work, fear of disclosure of HIV status for mother and child, parental perception that the child is healthy, and personal religious beliefs. Interpersonal factors like male partner nonparticipation, familial stigmatization and conflicts play a role as well. Community factors include accepted cultural norms, changing community dynamics, and perceived stigma; these factors, along with health care system factors such as the clinic location, lack of patient-centered care, delays at the clinic, and different appointment scheduling for mother and child contribute to non-adherence with medical visits [4].

Bastard *et al*. have defined an adherence indicator based on timeliness of clinic attendance [5]. The indicator is strongly predictive of virological response to ART and of the occurrence of drug resistance and identifies non-adherent patients in a timely manner in settings where viral load monitoring is not available [5]. Mortality in HIV-infected infants has significantly decreased in the era of effective ART, yet infrequent or sporadic clinic attendance and poor compliance with cotrimoxazole prophylaxis and/or ART in infants born to HIV-infected women and late presentation of infants identified after birth are major contributors to persistent childhood mortality [6]. Adherence with medical follow-up appointments is crucial for optimal treatment of chronic diseases, including pediatric HIV. The World Health Organization (WHO) encourages the use of new technologies to assist health delivery in resource-limited settings [7]. The use of mobile phone text message (SMS) and voice phone calls to enhance attendance at medical appointments shows a favorable effect on clinic attendance in the general population as well as among adults with HIV/acquired immunodeficiency syndrome (AIDS) [8]. There is also evidence from randomized controlled trials that mobile phone text-messaging at weekly intervals is efficacious in enhancing adherence to ART and in improving HIV viral load suppression [9]. Some studies on attendance of medical appointment have been conducted among adults and adolescents [10-17]. A recent Cochrane review concludes that appointment reminders sent via mobile phone text messaging (SMS) are as efficacious as voice phone call reminders in increasing patient attendance at medical visits and the effect is greater for both SMS and phone calls interventions as compared to no reminder [17]. These findings are similar to those of Hasvold *et al*. [18]. To our knowledge, the effect in developing countries of medical appointment reminders delivered by SMS, by mobile phone call, or by both SMS and phone call on clinic attendance of babies and children requiring HIV-related care has not yet been studied. The proposed trial, **mo**bile **re**minders for **Ca**meroonian children **re**quiring (MORE CARE) HIV treatment, aims to determine the reminder method that most increases pediatric patient attendance at medical appointments for treatment of HIV-infected and HIV-exposed children, and to determine which is the most efficient related to working time and financial cost.

### Trial design

We will carry out a 2 x 2 factorial, multicenter randomized controlled trial, single-blind with an allocation ratio of 1:1:1:1 for adult-child pairs to four groups. Group 1 will serve as the control group and is composed of subjects provided an appointment and no reminder, reflecting the usual standard of care. Group 2 subjects will be provided an appointment and an SMS reminder. Group 3 members will be provided an appointment and a voice phone call reminder. Group 4 members will be provided both an SMS and a voice phone call reminder. A schematic of the groups and a study diagram according to the recommendations of the Consolidated Standards of Reporting Trials (CONSORT) [19] are shown in Figures 1 and 2 respectively. The study will be performed for 5 months, from January to May 2013.

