### Randomization

Randomization assignments will be generated in blocks of four for each study site and will be allocated electronically using WinPepi version 11.25 [20]. After data collection of eligible subjects (adult-child pairs) who have given their consent, we will randomly assign participants into four groups. Allocation and randomization will be made centrally. In each block that is randomly pre-constituted, each subject (adult-child pair) will be allocated to one group.

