### Study objectives

The objective of this trial is to determine which reminder - SMS, phone call, or both SMS and phone calls - is the optimal method to increase HIV-infected and HIV-exposed children’s attendance at medical appointments (effectiveness) and which is the most efficient related to working time and financial cost (efficiency).

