#### Sample size

The primary objective is to measure the patient presence at their scheduled appointment. The calculation of the sample size will be based on the comparison of proportions of presence at appointment. The value of alpha is 0.05. The test is two-tailed. We assume that the presence at appointments using SMS as reminder and phone calls is, respectively, 59.0% and 59.6% [11]. We also assume that the difference would be 25% between the group that will receive both SMS and phone calls and the groups that will receive only an SMS or only phone calls. The minimum size of the sample required will be 50 subjects in each group for analysis by intention to treat with 80% power and a significance level of 0.05. We will exclude from analysis the participants with incomplete data. For this we assume a 10% attrition rate. Thus, we will need 224 subjects (56 in each group). WinPepi has been used to calculate the size of the sample [20].

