### Analysis plan

Data will be coded, entered, and analyzed using the Statistical Package for Social Science (SPSS) version 20.0 for Windows (SPSS, Chicago, Illinois, USA). We will describe continuous variables using means with standard deviations, and categorical variables using their frequencies and percentages. We will use the principle of ‘intention to treat’ analysis. The risk ratio will be used to measure effect of interventions on proportion of presence at medicals appointments and will be expressed with 95% confidence interval. The *t*-test will be used to compare quantitative variables, and the chi-square test will be used to compare qualitative variables. A *P* value less than 0.05 will be considered statistically significant. WinPepi will be used to measure the interaction between SMS and call in the group receiving both call back methods of appointment.

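### Attendance is tested without regard to the hospital blocks used in randomisation, and the sample size uses only one type of factorial contrast; a hospital-adjusted model with supplementary marginal effects would gain some precision at no cost in patients

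*Protocol article*

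**What the plan says.** - **Design.** Under Trial design: "We will carry out a 2 x 2 factorial, multicenter randomized controlled trial", with an "allocation ratio of 1:1:1:1 for adult-child pairs to four groups". Group 1 is control, Group 2 SMS, Group 3 call, Group 4 both.
- **Randomisation.** "Randomization assignments will be generated in blocks of four for each study site". Demographics and study sites lists three hospitals: urban, semi-urban and rural.
- **Objective.** Study objectives asks which of SMS, call or both "is the optimal method to increase HIV-infected and HIV-exposed children" attendance. The abstract's lead hypothesis is that two reminders beat one.
- **Sample size.** "The value of alpha is 0.05" and "The test is two-tailed". Assumed attendance is 59.0% with SMS and 59.6% with a call, and 25% higher with both. This gives 50 per group for 80% power, and 56 per group (224 in total) after 10% attrition. No control rate, main effect or interaction is stated.
- **Analysis.** The Analysis plan says "the chi-square test will be used to compare qualitative variables", with a risk ratio and 95% confidence interval for attendance. Table 1 gives the same test and adds synergy on additive and multiplicative scales. Neither place mentions hospital or says which groups or margins each test compares.

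**The concern.** Two features of the design are not carried into the named analysis of attendance.

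First, allocation is balanced within hospital. If attendance differs between an urban, a semi-urban and a rural hospital, a test that ignores hospital counts between-hospital variation as noise. It stays valid, but its standard errors are somewhat too large.

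Second, every participant in a 2 x 2 layout carries information on both reminders, yet the sample size considers only the combination against one reminder. Whether adding an SMS, or adding a call, raises attendance on average has no planned power and no named estimate. A service choosing an inexpensive reminder would want that estimate, and a non-significant result on about 50 v 50 could be misread as evidence that a reminder does not work.

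**Working it through.** **1. The stated sample size.** Inputs from Sample size: p1 = 0.59, p2 = 0.84 (25% read as absolute points), two-sided alpha 0.05, power 80%. With pbar = 0.715,

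n = [1.96 × √(2·pbar·(1 − pbar)) + 0.842 × √(p1(1 − p1) + p2(1 − p2))]² / (p2 − p1)²

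= [1.96 × 0.638 + 0.842 × 0.613]² / 0.25² = 50.0.

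For 59.6% v 84.6% the result is 49.3, rounded up to 50. Then 50/0.90 = 55.6, rounded up to 56, and 4 × 56 = 224. Power is 80.0% at 50 v 50 and 84.4% at 56 v 56. The stated size is therefore a two-group calculation between single cells, and it is correct for that contrast.

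**2. Gain from adjusting for hospital.** The article gives no attendance by site, so these rates are assumptions, with three equal sites and mean 60%. Unadjusted variance per participant is 0.60 × 0.40 = 0.240. Within-site variance is the mean of p(1 − p).

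| Assumed site rates | Within-site variance | Reduction |
|---|---|---|
| 55 / 60 / 65% | 0.2383 | 0.7% |
| 50 / 60 / 70% | 0.2333 | 2.8% |
| 40 / 60 / 80% | 0.2133 | 11.1% |

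**3. Size of the margins.** SMS: Groups 2+4 v 1+3. Call: Groups 3+4 v 1+2. Each is 2 × 56 = 112 v 112 randomised, or 2 × 50 = 100 v 100 evaluable.

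**4. Power with no interaction on the additive scale.** Each reminder adds d to an assumed control rate c. The two-cell contrast is c v c + d at 50 v 50. The margin is c + d/2 v c + 3d/2 at 100 v 100. Power uses the formula of step 1, solved for power.

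| c to c + d | Margin rates | 50 v 50 | 100 v 100 |
|---|---|---|---|
| 50 to 60% | 55 v 65% | 17% | 30% |
| 45 to 60% | 52.5 v 67.5% | 32% | 58% |
| 40 to 60% | 50 v 70% | 52% | 83% |

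**5. What the margin measures under the plan's own rates.** Take 59.0% (SMS), 59.6% (call), 84.0% (both) and an assumed control rate c. SMS alone adds 59.0 − c points. The SMS margin is 71.5 − (c + 59.6)/2. Additive interaction is 84.0 − 59.0 − 59.6 + c = c − 34.6.

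| c | SMS v control: points, power (50 v 50) | SMS margin: points, power (100 v 100) | Additive interaction |
|---|---|---|---|
| 35% | 24.0, 68% | 24.2, 94% | 0.4 |
| 45% | 14.0, 29% | 19.2, 80% | 10.4 |
| 55% | 4.0, 6% | 14.2, 56% | 20.4 |

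At 55% the margin averages 4.0 points without a call and 84.0 − 59.6 = 24.4 points with one: (4.0 + 24.4)/2 = 14.2. Its 56% power is not power for SMS against usual care.

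**6. Scale.** Interaction is zero on the additive scale at c = 34.6% and on the multiplicative scale at c = 0.590 × 0.596/0.840 = 41.9%. Between these, the same rates show positive additive and negative multiplicative interaction, so both scales are needed.

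**The case against.** A reader might infer that each reminder's effect is to be judged on 56 v 56, or that the factorial structure goes unused. The article supports neither. No section names the groups behind each chi-square test, and the same test and risk ratio could be run on the margins. Interaction is planned on both scales, the Discussion presents synergy as what the trial adds, and estimating interaction is a legitimate use of a 2 x 2 design.

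Nor do the margins answer the main question. Ranking three strategies and testing two reminders against one both need contrasts between single groups, and the sample size matches that hypothesis. The margin is a different quantity from single reminder v control, as step 5 shows. The SMS factor is also not uniform: under Reminder intervention the SMS goes out 72 hours before the appointment in Group 4 and 48 hours before in Group 2, so the SMS margin pools two timings. All of this stands, and it confines the margins to a supplementary role.

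Finally, hospital adjustment is often left to an analysis plan, and none is shown here. That limits the weight of the point but does not remove it, because the article names its test and effect measure for attendance and neither uses the strata. With SMS, call and their interaction all in the model, Group 4 v 2 and Group 4 v 3 gain precision only through the hospital term.

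**Conclusion.** The point holds as a modest improvement and does not show the planned analysis to be invalid. The named analysis of attendance ignores the hospital strata used in randomisation, and the sample size rests only on the combination against a single reminder. Adjusting for hospital gains about 1% to 11% of variance. That range depends on assumed site rates, and the upper end requires sites as far apart as 40% and 80%.

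The marginal effects would give each reminder's average effect on about 100 v 100 evaluable participants. For a 20-point effect from an assumed 40% control rate, power is about 83% against 52% for the two-cell contrast, provided there is no additive interaction. If control attendance is above about 45%, the plan's own rates imply an additive interaction of more than 10 points. The SMS margin then has less than 80% power and increasingly reflects Group 4.

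**What to change.** Keep Group 4 v 2 and Group 4 v 3 as the primary contrasts. Estimate their risk ratios with adjustment for hospital, either from one modified Poisson model with robust standard errors on all four groups (SMS, call, SMS x call, hospital) or by Mantel-Haenszel stratified by hospital.

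As a prespecified supplementary analysis, report the marginal SMS effect (Groups 2+4 v 1+3) and call effect (Groups 3+4 v 1+2), always beside the interaction on the additive and multiplicative scales already planned. State that these are average effects, that they do not replace single reminder v control, and that the SMS margin combines messages sent at 48 and 72 hours. Where interaction is evident, interpret the contrasts between single groups.

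The cost is analysis wording only: no more participants, no more data, and no change to the sample size. The drawback is that under synergy a reader may take a margin for the effect of one reminder used alone, so the caveat must accompany it.

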**Figure 1 F1:**
[figure not shown]
**Schematic of MORE CARE study groups.** We propose to enroll 224 adult-child participant pairs who will be randomized equally into four groups, as described in the text.

**Figure 2 F2:**
[figure not shown]
**Diagram of the study according to the recommendations of the Consolidated Standards of Reporting Trials (CONSORT) [**[19]**].**

### Randomization

Randomization assignments will be generated in blocks of four for each study site and will be allocated electronically using WinPepi version 11.25 [20]. After data collection of eligible subjects (adult-child pairs) who have given their consent, we will randomly assign participants into four groups. Allocation and randomization will be made centrally. In each block that is randomly pre-constituted, each subject (adult-child pair) will be allocated to one group.

### Blinding

The treating physician, the medical administrative assistant who will contact participants in Groups 2, 3, and 4 via mobile phone, the nurse (outcome assessor) responsible for recording patient presence or absence at the appointment, and analysts will be blinded. The participant will be received at the reception, and after giving his/her written consent, data will be collected by a nurse. The nurse will then send the following information to the medical administrative assistant: the identification code of the participant, date of appointment, the physician’s name, the phone number of the participant and the language of communication (French or English). A medical administrative assistant will then be responsible for carrying out all intervention: the sending of SMS and the calls to participants. The appointment will then be notified by the nurse of the reception. Before data analysis, we will assign a code for the four groups.

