### Reminder intervention

In the group receiving both SMS and phone calls (Group 4), the SMS reminder, in French or in English, will be sent between 08:00 and 12:00 AM, 72 hours before the appointment followed by a reminder phone call 48 hours before the appointment. The SMS will be sent manually. The SMS will serve as an appointment reminder and motivator. It will contain the date and the time of appointment, the location, and the name of the treating physician (Figure 3). To comply with medical confidentiality, the message will not contain any information on the health status of the child. Each text message sent will include about 300 characters including spaces. The method ‘message received’ will be used to ensure that the message was actually sent. For calls, a medical administrative assistant will phone 48 hours before the scheduled appointment, between 08:00 and 12:00 AM with communication in French or in English. A maximum of three calls attempts will be made. During the phone call, the medical secretary will remind the participant of the date and the location of his/her appointment and of the name of the treating physician. The name of the participant or the child will not be mentioned. In both SMSs and phone calls, communication is unidirectional towards the participant who cannot in return contact the medical secretary. This phone call procedure will be identical for the group receiving only phone calls (Group 3). Concerning the group receiving only the SMS (Group 2), the same procedure for sending SMS will be followed, and the SMS will be sent 48 hours before the appointment instead of 72 hours. It is important to note that, the content of communication (by SMS or by voice call) will be the same for all interventions.

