### Control

The control group (Group 1) will receive neither SMS nor phone calls, reflecting the usual practice of care.

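### The assistant who delivers every reminder cannot be blinded, and a group code alone does not blind analysts who hold the cost and working-time data

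*Protocol article*

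**What the plan says.** The Trial design section describes a "multicenter randomized controlled trial, single-blind with an allocation ratio of 1:1:1:1". The Blinding section gives that label its content by naming four roles: the treating physician, "the medical administrative assistant who will contact participants in Groups 2, 3, and 4 via mobile phone", the nurse who records presence or absence, "and analysts will be blinded".

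The same section then sets out the assistant's job: "A medical administrative assistant will then be responsible for carrying out all intervention: the sending of SMS and the calls to participants". The Reminder intervention section makes the schedule depend on the arm. Group 4 gets an SMS at 72 hours and a call at 48 hours, and Group 3 a call at 48 hours. For Group 2, "the SMS will be sent 48 hours before the appointment instead of 72 hours". Under Control, "The control group (Group 1) will receive neither SMS nor phone calls".

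For the analysts the article gives one measure: "Before data analysis, we will assign a code for the four groups". Under Primary outcomes and in Table 1, reminder cost and working time, and the ratios of attendance to them, are part of the primary outcome and are compared by t-test. An SMS is priced at 50 or 100 FCFA. The cost of a call is found from the change in the prepaid balance.

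**The concern.** Two of the four roles named as blinded are in doubt, for different reasons.

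The assistant chooses and delivers the reminder. That cannot be done without knowing the arm, so the statement describes a property the design cannot have. The same unblinded role produces the activity from which working time, a component of the primary outcome, is measured.

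For the analysts, a code hides the names of the groups but not their content. If the analysis file holds reminder cost and time beside attendance, the content can reveal the names. The abstract predicts that SMS alone will be the most efficient and the combination the most effective, so it matters whether those making analytic choices can tell which code is which. At stake are the accuracy of the blinding claim and the protection of analytic decisions, more than the recording of attendance.

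**Working it through.** **1. The assistant.** Setting the sections on delivery side by side gives:

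| Arm | SMS | Call | Reminder cost | Reminder time |
|---|---|---|---|---|
| 1 Control | none | none | 0 | 0 |
| 2 SMS | 48 h | none | 50 or 100 FCFA | writing to sending |
| 3 Call | none | 48 h | change in balance | first attempt to end of call |
| 4 SMS + Call | 72 h | 48 h | SMS price plus change in balance | both |

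The four rows require four different sets of actions from one role. Even among those sent an SMS, the sending time differs (72 h against 48 h). No one can carry out this table without knowing the row. The Blinding section therefore contradicts itself, and no arithmetic is needed.

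**2. The analysts, from the article's own figures.**
- Control: cost = 0 and time = 0 in every record. The ratio of presence to cost has a zero denominator and is undefined. The arm is recognisable at once.
- SMS only: cost takes only the values 50 or 100. The arm is recognisable unless every call were also billed at exactly those prices, which the balance-difference method does not suggest.
- Separate SMS and call fields: the pattern (none, SMS only, call only, both) identifies all four arms directly. The success-of-intervention outcome is also defined by different events for SMS and for calls, so delivery fields carry the same information.

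**3. The analysts, from total cost and total time only.** Separating Call from SMS + Call then needs call costs and unanswered-call rates, which the article does not give. Assumptions: call cost uniform on 20 to 400 FCFA; unanswered calls cost nothing; SMS price 50 or 100 with equal chance; 56 per arm. Rule: all-zero arm = Control; arm with only 50 or 100 = SMS; of the other two, the one with the lower minimum cost = Call, because every SMS + Call record costs at least 50.

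| Assumed share of calls unanswered | Simulated trials | All four arms identified |
|---|---|---|
| 0% | 2,000 | 100% |
| 10% | 2,000 | 100% |
| 30% | 2,000 | 100% |
| 50% | 2,000 | 100% |

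This result depends on the assumed call costs. The result for Control and SMS does not use them.

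**4. The synergy analysis.** On the additive scale the interaction is P(both) − P(SMS) − P(call) + P(control). To form it, one must know which two codes take the plus sign, and four arbitrary codes do not say. Coding alone therefore cannot cover this part of the efficacy analysis.

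**5. Sample size.** The pooled two-sided formula for 59.0% against 84.0%, alpha 0.05 and power 80%, gives n = [1.96·√(2·0.715·0.285) + 0.8416·√(0.59·0.41 + 0.84·0.16)]² / 0.25² = (1.251 + 0.516)² / 0.0625 ≈ 50. For 59.6% against 84.6% it also gives 50. Then 50/0.9 = 55.6, so 56 per group and 4 × 56 = 224, as stated. Blinding enters none of these inputs.

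**The case against.** The other side has several good points.

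- Whoever delivers a reminder must know its type, so correcting the label alters no result. True, but the article makes a positive statement that is wrong, and condensing a protocol into an article does not explain it.
- The order in which data are released to analysts commonly belongs to an analysis or data-management plan. That is fair as regards detail. The article does, however, state analyst blinding as a fact and gives coding as the means, and that means is insufficient once cost and time are in the file.
- Attendance is binary, is recorded by a separate nurse listed as blinded, and is to be analysed by a chi-square test and risk ratio named in advance. This stands, and it limits the damage to attendance.

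A reader might also infer more than the article supports:

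- That the reminders cannot be delivered, because the nurse's message to the assistant does not include the group. The Randomization section makes allocation central, so the group can reach the assistant by that route. The article simply does not describe the step.
- That the assistant times his or her own work. This is plausible, since the clock runs from writing or dialling, but the article does not say who does the timing.
- That cost is subjectively recorded. It already comes from the prepaid balance.
- That all four codes can be read with certainty. This holds for separate fields. From totals it rests on assumed call costs.

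**Conclusion.** The statement that the assistant is blinded is false as written. This rests only on the article's own text.

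The analyst part holds conditionally: coding alone does not blind analysts who hold cost and working-time data. Two of the four arms are recognisable from the article's own figures. All four are if SMS and call fields are separate, or, from totals, under the stated call-cost assumptions. The article mentions no separation of attendance from these data; if one exists in a document not shown, analyst blinding for attendance could stand.

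It would go too far to conclude that the single-blind label collapses or that the attendance result is biased. Blinding of the attendance nurse and of the physician is not contradicted by anything in the article. Any bias in attendance cannot be quantified from it and is probably small. The exposure lies mainly in the efficiency measures and in analytic choices. The text should be corrected and the data release ordered; no sample-size figure changes.

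**What to change.** 1. Remove the assistant from the list of blinded roles.
2. State that the group goes from central allocation directly to the assistant and does not pass through the nurse who records attendance.
3. Run and lock the between-arm attendance comparison on a file that holds only group code, site and attendance. Link the cost, time and delivery fields afterwards.
4. Do the synergy analysis with masked factor labels, or after unmasking. If the levels of each factor are masked as well, the sign of the additive contrast is settled only at unmasking.
5. Describe the trial as outcome-assessor and physician blinded, with analysts blinded for the attendance comparison only.
6. Where the phone log gives call duration, use it for call working time.

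The cost is changed wording, a two-step data release and a more modest blinding claim. No extra participants are needed.
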